# Statistical Analysis

Mixed models repeated measures analyses, with maximum likelihood estimation and an appropriate covariance structure, will be used to evaluate the efficacy of the Lifebuoy app relative to the control condition. The primary outcome is severity of suicidal ideation as assessed by the Suicidal Ideation Attributes Scale [SIDAS] over time (pre- test to post-test; pre-test to follow-up). The mixed models approach incorporates all available data, including participants with missing follow-up data points, under the missing- at-random assumption. Analyses will therefore accord with the intention-to-treat principle. This same approach will be used to examine reductions in secondary outcomes (depression (PHQ-9) anxiety (GAD-7) psychological distress (DQ-5) and wellbeing (SWEMWBS)) and tertiary outcomes (rumination (RTQ-10) insomnia (ISI) general mental wellbeing (SWEMWBS) help-seeking (GHSQ, CSRI)) over time.

Potential mechanisms of the symptom reduction will be measured by the changes in the levels of distress tolerance (DTS), loneliness (TILS) or suicide cognition (SGS). Negative life events (NLESS), grit (SGS) and questions about expectation of treatment success are included in the surveys as potential moderators. Participants’ current medications/interventions will be controlled for data analysis.

Descriptive statistics will be used to evaluate app engagement for participants in both conditions. Adherence will be indicated by the number of modules completed by participants. Participant module access and module completion will be automatically collected via the app. The mixed model approach will be used to determine whether adherence moderates the change in SIDAS scores over time in the intervention condition.

Acceptability of the LifeBuoy app will be examined through semi-structured interviews with a subset of participants and questionnaires in the survey. The interview data will be analysed using thematic analysis [40]. An inductive approach, independent of a theoretical confirmative method will be used to identify and group themes. The researchers will then refine the themes and determine the final coding framework. Discrepancies will be resolved by a third researcher to ensure reliability of the process.

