# Study Objectives and Hypotheses

## 1.1. Primary Aim

To assess the efficacy of the LifeBuoy app in reducing suicidal ideation in young people, as measured by the Suicidal Ideation Attributes Scale. Changes in suicidal ideation will be assessed by comparing the intervention and attention-matched (placebo) control conditions at baseline and post-intervention, and 3-month post intervention follow-up.

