## 1.4. Hypotheses

H1: Participants in the intervention condition will report greater reductions in suicidal ideation scores at post-intervention compared to the placebo control condition.

H2: Participants in the intervention condition will report greater reductions in depression and anxiety symptoms at post-intervention than the control condition.

H3: Higher levels of adherence to the LifeBuoy app will be associated with greater reductions in suicidal ideation at post-intervention.

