# Sample size

Based on a systematic review and meta-analysis [8], an effect size of 0.30 (Cohen’s d) will be expected between the intervention condition and the control condition at post-test in terms of suicidal ideation as measured by the SIDAS (Appendix C). Based on an attrition rate of 30% and a 0.50 correlation between pre- and post-test SIDAS scores, a sample size of n = 189 in each condition (total N = 378) will detect this expected effect size with power = 0.80 and alpha = 0.05. The planned sample size of n = 189 for the intervention condition will also allow statistical power of at least 0.80 to detect small-to-medium size effects in moderation analyses.

For the qualitative interviews we aim to recruit 10% of participants from the Intervention condition. This will result in a subsample of qualitative interviews of approximately n=20 persons based on a recruitment target of n=189 in each condition. In prior qualitative studies that have examined users’ experience with an app for managing psychological and physical health conditions, the sample sizes ranged from between 15 and 25 participants [41 – 43] which indicates our sample size is acceptable and justifiable.

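### The protocol is inconsistent on whether the primary SIDAS comparison is at post-intervention only or also at follow-up, and its alpha and power fit only the first.

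*Protocol*

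**What the plan says.** Two places in the protocol set the primary comparison at post-intervention only:

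- Section 1.4: "H1: Participants in the intervention condition will report greater reductions in suicidal ideation scores at post-intervention compared to the placebo control condition".
- Section 8 takes an effect of d = 0.30 "between the intervention condition and the control condition at post-test in terms of suicidal ideation as measured by the SIDAS". It assumes 30% attrition and a pre-post correlation of 0.50, and concludes that 189 per arm "will detect this expected effect size with power = 0.80 and alpha = 0.05". This is the only alpha in the document.

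Three places also include follow-up:

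- Section 1.1 compares the arms on suicidal ideation "at baseline and post-intervention, and 3-month post intervention follow-up".
- Section 7 defines the primary outcome as SIDAS severity "over time (pre- test to post-test; pre-test to follow-up".
- Appendix E (DSMB charter), objective 1, repeats the Section 1.1 wording almost unchanged.

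Section 3.1 adds that primary outcomes are assessed at T1 and then at T2. No section ranks the two contrasts, orders them, divides alpha between them, or says whether one or both must succeed.

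**The concern.** The primary comparison decides whether the trial is reported as positive, and this protocol describes it in two ways that do not match. Suppose T1 is null and follow-up favours LifeBuoy. H1 then fails, but Section 7 leaves room to argue that the primary outcome improved. In the reverse case H1 succeeds, but a reader of Section 1.1 could say that only half of the primary aim was met. If the text stays open, the choice could be made after the results are known, and nobody could check it against the protocol.

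The error rate and power are also at stake, because the figures in Section 8 are attached to one contrast at one time point.

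**Working it through.** **Inputs.** From Section 8: d = 0.30 at post-test, r = 0.50, attrition 30%, alpha 0.05, power 0.80, 189 per arm. Allocation is equal (Section 3.1). The protocol does not give the sidedness of the test, the correlation between the T1 and follow-up test statistics, or the effect and attrition at follow-up. The last three are assumptions here.

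**Reproducing 189 per arm.** With baseline adjustment the residual variance is 1 − 0.50² = 0.75 (in SD² units).

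- Normal formula: n = 2 × (1.960 + 0.842)² × 0.75 / 0.30² = 130.8, so 131 evaluable per arm, and 131 / 0.70 = 187.1, so 188.
- t-based: 131.8, so 132 evaluable, and 132 / 0.70 = 188.6, so 189.
- A one-sided test would give 149, so the plan's figure is two-sided.

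The sample size is therefore right for exactly one two-sided 0.05 test at T1. With 189 × 0.70 = 132.3 evaluable per arm, the mean of the test statistic is 0.30 / √(2 × 0.75 / 132.3) = 2.817, and power is Φ(2.817 − 1.960) = 0.804.

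**Rule A: either contrast may carry the claim, each at two-sided 0.05.** Under no effect, the family-wise error is 1 − P(|Z₁| ≤ 1.96 and |Z₂| ≤ 1.96), with Z₁ and Z₂ bivariate normal with correlation ρ.

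| ρ (assumed) | Any false-positive result | False claim favouring LifeBuoy |
| --- | --- | --- |
| 0 | 0.0975 | 0.049 |
| 0.3 | 0.095 | 0.048 |
| 0.5 | 0.091 | 0.045 |
| 0.7 | 0.083 | 0.042 |
| 0.8 | 0.078 | 0.039 |
| 0.9 | 0.070 | 0.035 |

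The nominal values are 0.05 and 0.025. Controlling the error under this rule with a Bonferroni split (0.025 each) would need 159 evaluable per arm, and 159 / 0.70 = 227.1, so 228 per arm. Keeping 189 per arm, power per contrast would be 0.718.

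**Rule B: both contrasts must succeed.** No alpha split is needed. Joint power is P(Z₁ > 1.96 and Z₂ > 1.96) with both means at 2.817. This carries d = 0.30, r = 0.50 and 30% attrition over to follow-up.

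| ρ (assumed) | Joint power at 189 per arm |
| --- | --- |
| 0.3 | 0.673 |
| 0.5 | 0.693 |
| 0.7 | 0.719 |
| 0.8 | 0.734 |

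**Date of the follow-up contrast.** Section 1.1, Section 5.2 and Appendix E (objectives and meeting schedule) put it at 3 months. Section 3.1 and the survey table in Section 6.5 put it at 4 months. The opening of Section 6.5 gives 4 months and day 182, with post-intervention on day 42. That is 182 − 42 = 140 days, or 20 weeks, after post-intervention, which is longer than either 3 or 4 months.

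**The case against.** The protocol can be read coherently. H1 is its only formal efficacy hypothesis on SIDAS, and it names post-intervention. Section 8 powers that same comparison with the only alpha given. The secondary aim and H2 follow the same pattern, with an aim that covers both time points and a hypothesis at post-intervention only. Section 1.1 lists baseline among its comparison times, so it may be a measurement schedule rather than an endpoint definition. The charter does not govern the efficacy analysis. Testing order and alpha allocation are commonly left to a statistical analysis plan, which is not at hand.

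Most of this stands, and it shows that T1 is the natural choice. It does not remove the mismatch, because Section 7 is the analysis section and attaches both intervals to the primary outcome itself. Which time point is primary is a protocol matter, and this protocol addresses it in two ways. An analysis plan that chose either version would still conflict with some of these sections.

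A reader might go further and infer that the trial has two unadjusted chances to claim its primary result, with the error rate nearly doubled. The documents do not support that. No section says that either contrast alone suffices. Section 7 describes one repeated-measures model and gives no decision rule, and a single condition-by-time test or a both-must-succeed rule would not inflate alpha. Nor may a reader infer that the sample size is wrong, since it is correct for the T1 test.

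**Conclusion.** The concern holds as an inconsistency about which time point decides the trial. The alpha and power in Section 8 are valid for the T1 contrast and for nothing wider. The figures for the two-contrast rules are conditional and mutually exclusive: a family-wise error of about 0.07 to 0.095 if either contrast sufficed, or joint power of about 0.67 to 0.73 if both were required. Neither rule is stated. Both results rest on an assumed correlation between the tests, and the power figure also rests on the same effect, pre-outcome correlation and attrition at follow-up as at T1. The conflicting follow-up dates add to the problem, because one of the two candidate primary contrasts has no settled time point.

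**What to change.** In Section 1.1, Section 7 and charter objective 1, and in Section 3.1 for consistency, name the between-arm difference in SIDAS at post-intervention (T1), estimated from the mixed model and tested at two-sided 0.05, as the single primary comparison. This matches H1 and Section 8, and 189 per arm then stands with power 0.804.

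Make the follow-up contrast secondary and report it as an estimate with its confidence interval. Its rank among the other secondary outcomes is for the trial team to decide, since the protocol sets no such hierarchy. Reconcile the follow-up date across Sections 1.1, 3.1, 5.2 and 6.5 and Appendix E.

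The change is to wording only, with no extra participants. The price is that a positive follow-up result on its own could no longer be called the primary result. If the team wants both time points to be primary, it must state the rule and re-power: for either-suffices with a Bonferroni split, 228 per arm (456 in total) under the assumptions above.

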# Sample size

Based on a systematic review and meta-analysis [8], an effect size of 0.30 (Cohen’s d) will be expected between the intervention condition and the control condition at post-test in terms of suicidal ideation as measured by the SIDAS (Appendix C). Based on an attrition rate of 30% and a 0.50 correlation between pre- and post-test SIDAS scores, a sample size of n = 189 in each condition (total N = 378) will detect this expected effect size with power = 0.80 and alpha = 0.05. The planned sample size of n = 189 for the intervention condition will also allow statistical power of at least 0.80 to detect small-to-medium size effects in moderation analyses.

For the qualitative interviews we aim to recruit 10% of participants from the Intervention condition. This will result in a subsample of qualitative interviews of approximately n=20 persons based on a recruitment target of n=189 in each condition. In prior qualitative studies that have examined users’ experience with an app for managing psychological and physical health conditions, the sample sizes ranged from between 15 and 25 participants [41 – 43] which indicates our sample size is acceptable and justifiable.

# Data Handling and Ownership

All research data collected during this trial is governed and handled following the Research Data Governance and Materials Handling policy. UNSW, rather than any individual or Organisational Unit, is the Custodian of data and materials and any information derived from the data. Original research data and primary materials generated in the research conducted at the University will be owned and retained by the University subject to any contractual, statutory, ethical, or funding body requirements.

## 9.1. Handling and Reporting Data

Principal Investigators are responsible for maintaining adequate and accurate source documents and trial records that include all pertinent observations on each site's trial subjects. Source data must be attributable, legible, contemporaneous, original, accurate, and complete.

Trial subjects will be assigned a unique participant ID following registration. Data reported on the case report form, derived from source documents, should be consistent with the source documents, or the discrepancies must be explained. Any change or correction to a case report form should be dated, initialled, and explained (if necessary) and should not obscure the original entry (i.e., an audit trail should be maintained); this applies to both written and electronic changes or corrections.

## 9.2. Direct Access to Source Data and Documents

Site principal investigator(s) and institution(s) will permit trial-related monitoring, audits, IRB/IEC review, and regulatory inspection(s), providing direct access to source data/documents.

# 9.3. Monitoring Quality Control and Quality Assurance

The Coordinating Principal Investigator and Principal Investigator(s) 'responsibility are to monitor the clinical trial. The Coordinating Principal Investigator and Principal Investigator(s) are responsible for undertaking or participating in site initiation or protocol-specific training before recruitment and data collection commences. A monitoring report demonstrating regular compliance monitoring with the clinical trial protocol, procedures is provided to the UNSW HREC annually.

Root, cause, analysis reports are to be completed by the Coordinating Principal Investigator for reports of non-compliance and serious breaches. A corrective and preventative action plan must be developed and actioned for any reports of non-compliance and serious breaches.

# Safety and Monitoring

## 10.1. Assessment of Adverse and Safety Events

All adverse events and safety issues will be reported as per the Safety Monitoring Reporting Guidelines for Clinical Trials set out by the UNSW Human Research Ethics Committee. All adverse events and serious adverse events defined below will be reported by the Coordinating Principal Investigator to the Data Safety Monitoring Board (DSMB) and the UNSW Human Research Ethics Committee using the guidelines indicated in Table 2.

a. Known Adverse Effects

An individual scoring above 20 on the SIDAS will be considered an expected adverse event (given the study population has a history of recent suicidal ideation).

b. Known Harms, Risks or Discomforts

- Anxiety induced by answering a questionnaire and/or engaging in therapeutic activities on the app at the end of the data collection phase. There is a moderate likelihood and low severity of this discomfort occurring, given the more than low-risk population participating in the study.
- Psychological harms, including feelings of distress or anxiety, for example, due to disclosure of sensitive information on questionnaires and/or engaging in therapeutic activities on the app. There is a moderate likelihood and low severity of this discomfort occurring, given the more than low-risk population participating in the study.

10.2. Adverse Events or Adverse Reactions

Adverse events (AE) are considered any untoward medical occurrence in a patient or clinical trial participant administered the intervention, which does not necessarily have a causal relationship with this treatment.

AEs are assessed using the safety monitoring flow chart. Those classified as "not serious" are assessed by the research team’s qualified clinical expert. The clinical expert cannot delegate this responsibility to other research personnel.

Adverse event reports must be reported to the Coordinating Principal Investigator within 24-hours of notification. All adverse event reports must be recorded in the UNSW Safety Monitoring Register Template (Appendix D).

## 10.4. Significant Safety Issue (SSI)

A safety issue that could adversely affect participants' safety or materially impact the trial's continued ethical acceptability or conduct. The Human Research Ethics Committee must be notified of all significant safety issues within 15 calendar days of the sponsor instigating or being made aware of the issue**.** SSI reports must be recorded in the UNSW Safety Monitoring Register Template.

[figure not shown]

Figure 2. Safety Assessment Flow Chart Investigational Medical Product Trials

# Non-compliance, Protocol Deviation and Serious Breaches of Good Clinical Practice

## 11.1. Protocol Deviation

A protocol deviation is defined as any breach, divergence or departure from the requirements of Good Clinical Practice, the clinical trial protocol, the clinical trial standard operating procedures, or the human ethics approval that does not have a significant impact on the continued safety or rights of participants or the reliability and robustness of the data generated in the research or clinical trial. Protocol deviations are events that do not occur persistently or systematically and do not potentially result in participant harms. Examples of protocol deviations include but are not limited to:

- Deviations because of participant adherence to the protocol, including rescheduled study visits, participants refusal to complete scheduled research activities or failure to complete self-report questionnaires required by the study protocol.
- The completion of consent forms, safety monitoring report, case report forms or data collection tools in a manner that is not consistent with the protocol instructions or failure to make reports within the required reporting timeframes.
- Administration of the clinical trial investigational medical product or device in a manner that is not consistent with the manufacturer's instructions for use.
- Use of an unapproved version of the participant information statement or recruitment of participants using unapproved recruitment procedures.
- Inclusion of a participant that does not meet the inclusion criteria.
- An urgent safety measure must be taken to eliminate an immediate hazard to a participant's health or safety.

## 11.2 Serious Breach of Good Clinical Practice

A serious breach is defined as a breach of Good Clinical Practice, the clinical trial protocol, the clinical trial standard operating procedures, or the human ethics approval that is likely to affect to a significant degree the safety or rights of participants or the reliability and robustness of the data generated in the clinical trial. Examples of serious breaches include but are not limited to:

- Persistent or systematic non-compliance with the instructions for completing consent forms, safety monitoring or data collection tools that result in continued missed or incomplete data collection.
- Failure to record or report adverse events, serious adverse events, or significant safety issues where urgent safety measures were implemented.
- Widespread and uncontrolled use of protocol waivers affecting eligibility criteria, which leads to harm to trial subjects.
- Failure to conduct research following the issued approvals, permits or licences by required laws, regulations, disciplinary standards, and UNSW policies relating to the responsible or safe conduct of research.
- Concealing or facilitating breaches (or potential breaches) of the Research Code by others.
- Researching without the requisite approvals, permits or licences required by laws, regulations, disciplinary standards, and UNSW policies related to the responsible or safe conduct of research.
- Failure to conduct research as approved by an ethics review body where that conduct leads to (or has the potential to) results in participant harms.
- Researching without ethics approval as required by the National Statement on Ethical Conduct in Human Research where that conduct leads to (or has the potential to) result in participant harms.
- Any breaches as outlined in the UNSW Research Misconduct Procedure or the Australian Code for responsible conduct of research that leads to (or can potentially) result in participant harms.

## 11.3. Reporting Protocol Deviations

- Protocol deviations occurring at a site must be documented in site files and reported by the principal site investigator to the Coordinating Principal Investigator.
- The Coordinating Principal Investigator must review the protocol deviation and the clinical trial protocol to establish the corrective actions and preventative steps to prevent the deviation from reoccurring.
- The protocol deviation and corrective action plan must be reported to the UNSW Sponsor's Delegate by the Coordinating Principal Investigator or Coordinating Research Team using the protocol deviation report form.

## 11.4. Reporting of a Serious Breach

- The Coordinating Principal Investigator must review the serious breach, along with the clinical trial protocol, to develop a Corrective and Preventive Action (CAPA) that defines the steps to prevent the serious breach from reoccurring.
- The serious breach report and the CAPA must be provided to the approving HREC, and the UNSW sponsors delegate for review and approval.

## **11.5.** Review of a Protocol Deviation and a Serious Breach

- The UNSW HREC will review reports to establish whether the event meets the definition of a protocol deviation or serious breach, establish whether the proposed CAPA is appropriate and establish whether there is or will be ongoing impact reliability and robustness of the data generated.
- Protocol deviation or serious breach reports where a UNSW researcher, staff or student is responsible for the protocol deviation or the serious breach will be reviewed as per the [UNSW Research Misconduct Procedure](https://www.gs.unsw.edu.au/policy/documents/researchmisconductproc.pdf) to establish a breach of the [UNSW Research Code of Conduct](https://www.gs.unsw.edu.au/policy/documents/researchcode.pdf) has occurred.

